## Abstract

**Background:**

Physical activity (PA) is not only an important marker of physical impairment, but also a pathway to improve quality of life and enhance cognitive and social functioning of old individuals. Yet, making interventional use of PA training as a means for prevention and enhancement of quality of life of nursing home residents has found very limited attention worldwide so far. That said, the project ‘Long-term Care in Motion’ (LTCMo) as a part of the INNOVAGE consortium (funded by the European Commission) has the following aims: Overall: Install and assess a socially innovative intervention in the nursing home ecology. Concrete: (a) Conceptualization of a multidimensional intervention program (resident and staff oriented) with the potential to promote PA in nursing home residents; (b) Mixed-methods assessment of the program based on automated recording as well as questionnaire data.

**Methods/Design:**

LTCMo’s PA-related intervention has several components which are applied in parallel manner: (1) Residents are engaged in a physical exercise program that is based on multiple approaches: supervised group sessions, a serious games approach, and specific training in severely impaired persons; (2) Staff members will receive a competence training with a focus on PA motivation and facilitation of residents’ PA engagement. Primary outcome assessment (movement-related behavior of residents) is completely conducted by means of automated data collection strategies (accelerometer-based activity recording, sensor-based life space recording). This is enriched by a broad range of secondary outcomes (e.g., cognitive performance, depression of residents; behavioral and attitudinal components of staff). Pre-, post- and 3-month follow-up assessment will take place in the target intervention setting as well as in a waiting control condition in which we will also replicate the training and its assessment in a later step.

**Discussion:**

Although we are faced with methodological challenges (e.g., rather small sample size; no randomized control trial), we believe that our approach has something to offer and indeed has some unique characteristics that may have the potential to contribute to the enhancement of nursing home residents’ quality of life and at the same time further PA-related research with vulnerable populations at large.

**Trial registration:**

Current Controlled Trials ISRCTN96090441. Registered 31 July 2014.

## Background

Nursing home residents are characterized by old age, high prevalence of multi-morbidity, frailty, mobility impairment, severe cognitive deficits, and depression [1]. In terms of day-to-day behavior, an essential feature of nursing home residents is their very low physical activity (PA), even compared to non-institutionalized older adults in advanced old age [2], although there is also a subgroup depicting excess motor activity and wandering behavior [3]. However, PA is not only an important marker of physical impairment, but also a major pathway to improve quality of life and to enhance motor, cognitive, and social functioning in old age. Empirical evidence supports rather large positive effects of PA on a range of important endpoints such as cardio-vascular fitness, gait and balance, fall reduction, cognitive function, and well-being in the general older population [4, 5]. Moreover, PA training has revealed sizable positive effects in terms of physical and functional ability-related endpoints in those with dementia-related disorders, if efficiently tailored in its application format to the remaining competencies of this specific group [6]. Regarding the nursing home situation, a number of intervention studies, particularly those focusing on intensive muscle training, have shown positive effects in terms of fall reduction [7]. Beyond the fall-related literature, a recent review [8, 9] found only 12 intervention studies—though with mixed design qualities—that are able to speak on the effects of PA training in nursing home residents. Although this scarce empirical platform partially supports the assumption of positive effects of PA on a number of endpoints such as increased motor behavior and activity at large, the overall empirical evidence in this area has remained limited and inconclusive.

At the practical and implementation level, a number of barriers making the exertion of PA difficult for nursing home residents have been identified [10]. Residents’ low physical and cognitive health and functional status including gait and balance problems and sensory impairments likely hinder residents to imagine that a considerable increase in their PA is possible and feasible without taking too many risks. For the same reasons, staff may refuse to think about encouraging residents to be physically active. Indeed, an intervention to increase PA may increase risk exposure and falls, especially in residents with advanced motor impairment [11]. Psychologically, following the classic idea of ‘total institutions’ originally described by Goffman [12], many nursing home residents may feel powerless and low in self-efficacy. In addition, staff may have a tendency for dependency-enhancing behavior regarding residents, thus possibly helping too much and fostering independent behavior too less [13]. All in all, these barriers may result in a vicious circle, in which an overall sedentary life style in the nursing home ecology is reinforced because of a variety of reasons, which may lead to additional impairment in functioning in the longer run via disuse processes and a situation of low engagement at large in everyday life [14].

In research terms, a major difficulty of studies on PA conducted in nursing homes lies in the rigorous assessment of PA. In order to assess changes in PA as the consequence of a respective intervention in a reliable and valid way, subjective measures (e.g., interviews, structured questionnaires) may be hampered due to a decline in cognitive abilities or presence of cognitive impairment like dementia, resulting in recall and response biases. Furthermore, especially nursing home residents tend to be engaged in low intensity activities and PA frequently is of short duration and operating on an irregular basis, i.e., short and slow walking episodes are more the rule than the exception. This situation challenges reliable recall processes, particularly in questionnaire-based research [15, 16].

Therefore objective assessment by high resolution automated activity recording seems mandatory. In addition to quantitative and increasingly also qualitative assessment of PA, ‘life space’ assessment has evolved as an important complementary research perspective. PA assessment includes objective documentation of frequency, duration, and temporal course, of movement characteristics such as lying, sitting, standing and walking. Qualitative data analysis including risk of falling, number, duration, and qualitative features of standing, walking, and transfer actions become increasingly technically feasible. The life space concept, originally questionnaire-based [17], has found its automated recording extension by using sensor installations in the target physical ecology [18], allowing for objective assessment of the physical-spatial context, in which movements take place (e.g., frequency and duration of use of public vs. private locations). The combination of both of these assessment strategies hold promising and complementary research options which have, to our knowledge, not been used in the nursing home ecology so far.

Finally, the kind of PA intervention has to be determined that suits the requirements of the nursing home ecology best, given the range of barriers as described above [19]. Although it seems reasonable to rely on the overall positive evidence and practical experiences gathered with classic PA-enhancing training modules applied to vulnerable older populations such as people with dementia (PWD [6]), additional training components may be advisable. In particular, it may be helpful in motivational as well as stimulus enrichment terms to consider new, creative, and fun-evoking training procedures that may particularly suit nursing home life. For example, training strategies based on a ‘Serious Games’ approach may be a promising addition to focused PA group training programs [20]. Such game-based training typically addresses both motor and cognitive performance. For example, a music-supported stepping task may focus on dynamic postural control, which is mandatory for motor key features such as standing or walking and represents the most effective training approach with respect to fall prevention in older persons [21]. Cognitive training elements of Serious Games-based PA training may relate to cognitive sub-performances such as temporo-spatial orientation, executive functions, timing/reaction time, action in inhibition, attention-related motor cognitive (dual-) tasks, representing important features for motor control and early markers of cognitive decline. Furthermore, given the critical role of staff in the nursing home ecology, it seems helpful to back a direct nursing home residents-oriented PA intervention with staff-based training elements which focus on the significant role of staff as motivational and PA-reinforcing agents [13, 22].

In sum, although PA-related training strategies have considerable potential to enhance quality of life of nursing home residents and potentially also enrich the nursing home as a professional work environment, the respective research literature is very limited. This is where the project ‘Long-term Care in Motion’ (LTCMo) starts from.

### Project aims

LTCMo is part of the INNOVAGE consortium funded by the European commission [23]. In line with the major focus of the European Commission to raise Healthy Life Expectancy (HLE) and overall quality of life of older adults, INNOVAGE aims to showcase a range of social innovations able to contribute to this overarching goal. Within the INNOVAGE architecture, LTCMo addresses the situation of the highly vulnerable older nursing home population and aims to install and assess a respective socially innovative intervention in the nursing home ecology. Driven by the idea of a ‘natural lab’, we are heading for a procedure that comes with innovative and—compared to previous research—significant improvements in terms of its intervention approach as well as its assessment concept. Study aims include:Conceptualization of a multidimensional intervention program operating at different levels of the nursing home ecology with the potential to promote PA behavior in nursing home residents intensively involving residents as well staff members and by these means efficiently counteracting the existing barriers which typically prevent PA exertion.Development of an innovative assessment strategy to comprehensively assess residents’ PA behavior as well as intervention effects, respectively. This assessment concept represents the natural lab component of LTCMo’s social innovation and makes an attempt to unify a practical and hopefully quality of life-enhancing strategy (i.e., the multidimensional intervention) with an ambitious and innovative research and measurement concept in the nursing home setting. The assessment concept as a whole is envisaged to be as reliable, valid, cost-effective, and unobtrusive as possible. 2.1.Residents’ habitual PA behavior is comprehensively depicted using objective assessment methods, i.e., accelerometer and life space sensor-based data.2.2.Assessment of the intervention effects should include pre-, post-, and 3-month follow-up measurement occasions to estimate the short and long-term effects of the intervention in exemplary manner. There is a waiting control condition consisting of a second nursing home ecology, in which at the first stage of assessment no intervention program is conducted to document the natural course without interventional effects.Disseminate findings as intensively as possible based on a guidebook containing a detailed description of the intervention program as well as findings and practical recommendations able to enhance the implementation process of the intervention in nursing home ecologies at large.

## Methods/Design

### Description of intervention

LTCMo’s PA-related intervention has multiple components which are applied in parallel manner: (1) Residents engage in a physical exercise program that is based on multiple approaches: supervised group sessions, a serious games approach, and specific training in severely impaired persons. Its bottom line is a rigorous focus on functional and strength exercises to improve key motor qualifications necessary for mobility, autonomy, and motion security, i.e. standing, walking, sitting down and standing up. It suits as much as possible the needs of the fragile nursing home population; (2) Staff members receive a competence-enhancing training with a focus on PA motivation and facilitation of residents’ PA engagement. To permanently maintain intervention effects, staff is trained to implement training strategies in daily NH routine.

#### Physical exercise training

The exercise intervention of LTCMo relies on long-standing experience and existing evidence of successful PA interventions in old, multimorbid adults with and without cognitive impairment [6, 24, 25] and is at the same time specifically tailored to the needs of the target population of physically and cognitively impaired nursing home residents. The supervised training programs used in this study significantly increased functional and cognitive performance and did not lead to adverse events, neither in long-term use in comparable clinical settings nor in previous intervention studies of the research group [6, 24, 25].

*Supervised group sessions & Specific training in severely impaired persons.* The 45-minute sessions are offered twice a week over a 12-week period in small groups of four to eight residents. Training intensity is increased according to individual progress. To ensure homogeneity, group composition is determined according to residents’ motor and cognitive status, i.e., based on impressions and results derived from performance-based tests and cognitive screening at baseline testing. The exercise sessions are supervised by trained sports scientists to support motivation/adherence and to prevent adverse events such as falls. Trainers are instructed to use communicational strategies developed for use in patients with cognitive impairment. Residents with distinct behavioral problems resulting in disturbance of exercise activities or residents with advanced postural deficits are not included in exercise group sessions. However, they are still eligible for an individual training (Specific training in severely impaired persons) which is based on exercises used in the group training and adapted to the individual abilities of the participants in a one-to-one training situation.

*Serious Games Approach.* In general, exercise training is based on repetitive and standardized training tasks, which guarantee effectiveness, but may fail to attract all participants. The serious games approach provides an alternative mode to motivate these persons to be active with high effectiveness, supported by a “serious”, evidence-based exercise task. The game is constituted as a dual motor/cognitive task. The motor task is based on a progressive functional task (stepping/dynamic postural control) representing the most effective training target for fall prevention [21, 26, 27]. The cognitive task targets different cognitive sub-performances such as divided attention, temporo-spatial orientation, reaction time, and executive performances, which are early markers of cognitive decline [28] and risk factors for falls [26, 27, 29]. For part of such cognitive tasks, trainability has been proven [25].

In the current study we use a stepping video game which is based on a modified version of “StepMania dance and rhythm game” [30], see Figure 1. It is constituted as a cognitive-motor training in which the exercise character is substituted by a game character. It will be conducted in small groups of 3-4 residents with only one person playing at a time, supervised by a sports trainer or a trained research assistant. To play the game, the participant has to stand on a dance plate which is connected to a computer via USB. The dance video game screen is projected on a TV screen. A scrolling display of squares moving up, down, right, or left across the screen cues each move and participants have to execute the indicated steps (forward, backward, right, or left) when the squares reach corresponding squares at the top, bottom, right, or left side of the screen (see Figure 1). Participants will have to alternately perform 10 levels of 90 seconds duration each. Difficulty is individually tailored as the program depends on previous individual performance level to prevent overtaxing of users. The standardized program was adjusted to the performance level of frail older adults with and without cognitive impairment in pilot testing prior to the intervention.

**Figure 1 Fig1:**
[figure not shown]
**Screenshot of the game and stepping platform [**
[30]
**].**

#### Physical activity-enhancing competence training for staff

The major aim of the staff centered PA-enhancing competence training is to enable staff members to interact with residents in a way that encourages their PA as much as possible. The conceptual background of the staff training is based on established models of the role of person-environment interactions in long-term care institutions and the significant role of staff [22, 31] as well as on psychological models of health psychology (e.g., Self-Determination Theory [32]); Theory of Planned Behavior [33]; Health Action Process Approach [34], self-regulation theory (e.g., Social Cognitive Theory [35]); model of selective optimization with compensation [36]; dependency-support script [13]); life-span motivational models (e.g., Socioemotional Selectivity Theory [37]); positive messaging [38]). Staff members receive intensive information on the role and evidence related to PA in later life and also regarding the role of negative aging stereotype and concomitant underestimation of residents’ remaining competencies (e.g., [39]). Emphasis is also put on the importance of barriers and facilitators of being physically active and on ways to overcome such barriers in most creative ways. To achieve this goal, staff learns how to use communication and interaction techniques able to encourage residents to be more active (e.g. positivity, motivational interviewing; see also conceptual background above). Based on role play technology and bed-site trainings, staff intervention is also enriched by extensive practice opportunities. In addition, the practical application of communication strategies in caring routines with the goal to develop strategies for upcoming challenges and to monitor the achievement via feedback-loops is a major issue in the later part of the training program and intents to increase the transfer of what has been learned to day-to-day interactions with residents.

The staff training component is served within the framework of the existing regular in-house training schedule and comprises a total of 12 sessions with one session weekly thus amounting to a duration of approximately three months: Eight 1-hour-sessions including theoretical as well as practical contents and four 30-minutes-sessions mainly serving as case discussions. Each session is offered twice a week to facilitate staff attendance due to their revolving shift involvements. An overview of the full program is given in Table 1. Training sessions are planned for a group format of 15 to 20 persons.

**Table 1 Tab1:** **Contents and sequential flow of the PA-enhancing competence training for staff**

Session	Content
1	Introduction and overview over training program
2	Importance of physical activity in (old) age: Theoretical input and joint discussion
3	The art of behavior change: Theoretical input and joint discussion
4	The role of age stereotypes in caring routines: Theoretical input and joint discussion
5	Communication strategies I: Theoretical input and practical exercises
6	Communication strategies II: Theoretical input and practical exercises
7	Communication strategies III: Practical exercises
8	Feedback on practical application of communication strategies in caring routines and development of respective solutions
9	Case discussion and development of respective solutions
10	Case discussion and development of respective solutions
11	Case discussion and development of respective solutions
12	Case discussion and development of respective solutions

### Research design and sample recruitment

Figure 2 depicts our research design. We conduct a quasi-experimental pre-post-assessment study with baseline measurement (T1), measurement at the end of the intervention period (T2), and measurement at the end of a 3-month follow-up (T3) in two nursing homes in the Heidelberg area (Germany). In one nursing home a run-in period (T0) will be conducted, documenting status and course without intervention (T0 vs. T1). One nursing home serves as target intervention facility, whereas the other serves as a waiting control condition. Inclusion criteria for residents’ assignment to the intervention are:Permanent resident in included nursing homesWritten informed consent (resident/legal representative)For participation in exercise sessions: Ability to stand (supervised group training) or ability to walk (stepping video game). Residents not fulfilling this criterion are still eligible for participation in the assessment procedure.

**Figure 2 Fig2:**
[figure not shown]
**Study design.**

Exclusion criteria for residents’ intervention participation are:Short-term resident in one of the two nursing homesBehavioral problems resulting in disturbance of exercise activities (with respect to participation in group sessions only).

For residents with severe motor impairment (supervised ability to stand) and challenging behavior, training with one-to-one supervision will be established.

All staff members willing to participate are eligible for inclusion. Residents and staff members not willing to participate in the intervention, but providing informed consent and willing to provide pre- and post-assessment information may be used later as a ‘natural’ control group component in addition to the planned control condition.

As this project has the ambition to assess residents in a ‘natural lab ecology’ of two nursing homes as comprehensively as possible and to include a relative maximum of residents based on our specific approach, we refrain from any formal power calculation. However, we made sure by selecting two homes with more than 100 residents each that complete assessment of at least 50 participants per home will be possible, assuming a drop-out rate of about 50%. Hence, we currently expect about 50 residents in the target intervention setting and about 50 in the waiting control condition. In addition, we expect about 20 staff members to become part of the staff training component and a similar magnitude to serve as controls.

Prior to the onset of the intervention, assessments in terms of self-reports, proxy ratings, performance-based measures, accelerometer, and life space sensor-based data as well as staff data (self-reports only) are conducted (T1). In both facilities, a small group of three staff members is trained to provide the proxy ratings for *all* participating residents (inter-rater reliability will be examined). In the intervention facility, assessments will take place in the final week of the intervention period (PA and life space assessments only) in order to analyze direct effects of the intervention on PA, immediately after the intervention period has been completed (T2), as well as three months after completion of the training (follow-up, T3) by the comprehensive assessment battery. In the waiting control facility, baseline assessment (T0) is followed by a run-in period to document the natural course without intervention. The assessment protocol for the following intervention and post-intervention phase is otherwise identical to the protocol as described above for the first intervention facility.

The process analysis addresses the setting conditions, implementation, and receipt of the intervention as well as its feasibility. Several means of a process analysis are employed to assess the sampling and intervention quality, e.g., characteristics that may cause selective sampling of participants (e.g., residents’ depressive symptoms) are documented as well as the frequency of participation, questionnaire-based evaluations of each staff training session, and supervision of staff’s application of learned techniques. The effect analysis addresses the effectiveness of the intervention components regarding the described outcomes.

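### Residents who decline the intervention may later serve as an extra 'natural' control group, although they are self-selected and, in the target home, exposed to the trained staff

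*Protocol article*

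**What the plan says.** The design has one home per condition, without randomisation: "One nursing home serves as target intervention facility, whereas the other serves as a waiting control condition". After the eligibility criteria, the same section (Research design and sample recruitment) adds a further option. It concerns residents and staff "not willing to participate in the intervention, but providing informed consent and willing to provide pre- and post-assessment information may be used later". The role foreseen for these people is to serve "as a ‘natural’ control group component in addition to the planned control condition".

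Staff training is the second of two intervention components (Description of intervention): "Staff members receive a competence-enhancing training with a focus on PA motivation and facilitation of residents’ PA engagement". The same section adds that "staff is trained to implement training strategies in daily NH routine". The section on the competence training gives its main aim as to "enable staff members to interact with residents in a way that encourages their PA as much as possible". Under Secondary outcome measures: staff, the training is again described as intended to act on residents' PA, and PA is a primary outcome.

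The process analysis will document characteristics that could make participation selective, with depressive symptoms as the example. No adjustment for them is stated.

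**The concern.** A control group should show what would have happened to participants without the programme. Target-home refusers fail this in two ways.

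- **Selection.** Refusal itself defines the group. Willingness to train is plausibly tied to motivation to move and self-efficacy, which the protocol lists as possible moderators, and to depressive symptoms, which it names as a possible source of selective sampling.
- **Exposure.** Trained staff care for the whole home, and nothing confines their new practice to residents who agreed to train. A target-home refuser can therefore receive one of the two components while being counted as a control.

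No section acknowledges this exposure or limits how the group may be used. In a study with one home per condition and about 50 residents in each, a later free choice of controls could change the result.

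**Working it through.** **1. The plan's own figure.** More than 100 residents per home with about 50% drop-out gives 100 × (1 − 0.5) = 50, which agrees with the stated minimum of 50 per home. No stated number depends on refusers. The plan does without a formal power calculation and gives no effect size or SD, so every effect-size input below is an assumption.

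**2. Who is exposed, and when.**

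| Refusers in | Period | Self-selected | Exposed to trained staff |
|---|---|---|---|
| Target home | from start of programme | yes | yes, in part |
| Waiting home | T0 to T1 (run-in) | yes | no |
| Waiting home | after T1 | yes | yes, in part |

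Exposure is partial because only willing staff, about 20, are trained.

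**3. Form of the bias.** Let τ be the full programme effect in SD units, s the share of it that reaches refusers through staff, and b the difference in change between willing and unwilling residents without any programme. Participants minus target-home refusers then estimates τ + b − sτ, so the bias is b − sτ. Take τ = 0.5 and s = 0.4, so sτ = 0.20:
- b = 0: bias −0.20 SD
- b = 0.2: bias 0
- b = 0.4: bias +0.20 SD

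The document fixes none of τ, s and b, so the sign is open.

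**4. Consequence if refusers are the sole comparator.** Assume 50 against 50 and a two-sided 5% test. The standard error is √(2/50) = 0.20 SD, and power is approximately Φ(d/0.20 − 1.96).
- Exposure only (b = 0), with s = 0, 20, 40, 60%:
  - τ = 0.5: contrast 0.50, 0.40, 0.30, 0.20 SD; power 0.71, 0.52, 0.32, 0.17.
  - τ = 0.8: contrast 0.80, 0.64, 0.48, 0.32 SD; power 0.98, 0.89, 0.67, 0.36.
- Selection only (τ = 0), with b = 0, 0.2, 0.4, 0.6 SD: rejection rate 0.05, 0.17, 0.52, 0.85.

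**5. When the planned comparison is touched.**
- *Pooling.* If a fraction f of the control group is target-home refusers, the control mean shifts by f(sτ − b). Assume 20 refusers join 50 waiting-home residents: f = 20/70 = 0.286. With s = 0 and b = 0.2 to 0.5, the control mean falls by 0.286 × 0.2 = 0.057 to 0.286 × 0.5 = 0.143 SD. With b = 0 and s = 25 to 50%, 0.286 × 0.25 = 7% to 0.286 × 0.5 = 14% of the effect is lost. With f = 0 there is no shift.
- *Removal.* Let g be the share of unwilling residents, and assume g and b are equal in both homes. Dropping refusers from the target home only gives τ + gb. Keeping them gives τ[1 − g(1 − s)], which is free of b. With g = 0.286, τ = 0.5, s = 0.4 and b = 0.2, dropping gives 0.5 + 0.057 = 0.557 SD, and keeping gives 0.5 × (1 − 0.286 × 0.6) = 0.414 SD.

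**The case against.** The strongest reply is that the option is both optional and supplementary. The planned control is the waiting home, the expected numbers are set without refusers, and the wording fits a separate descriptive third group as well as a pooled one. The article also concedes that it is not a randomised trial, calls itself a demonstration study and asks for replication in a stronger design. Selection characteristics are documented. This reply stands as far as weight is concerned: as written, the planned comparison is not compromised.

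It does not remove the defect. Calling a group a control, even an additional one, invites an effect contrast. The article's own list of limitations mentions neither the selection of refusers nor their exposure to trained staff. Documenting selection does not adjust for it, and the Discussion says that component effects will not be separated, so the article states no means of estimating the exposure.

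A reader might infer stronger points, which the text does not support:
- *That refusers receive half the programme.* Staff training is one of two components, but no share of the effect is given and only some staff are trained.
- *That the bias favours the programme.* Its sign depends on b and sτ, as shown above.
- *That only volunteers remain on the treated side.* Residents who cannot stand stay eligible for assessment, and nothing restricts the target-home analysis group to exercisers.
- *That the plan expects selection on depression.* It says only that such characteristics may cause it.

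**Conclusion.** The point holds in a limited form. Residents who decline are a self-selected group and, in the target home, a partly treated one, so they cannot serve as a control for the effect analysis. Waiting-home refusers are unexposed during the T0 to T1 run-in but are still self-selected. The two biases can oppose each other, and the document gives no basis for signing or sizing the net error. The figures above show only what assumed inputs would imply, and the pooled ones also assume a merger that the text does not state.

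A reader might conclude that the main comparison is invalid. That does not follow: it is affected only if refusers are pooled into the waiting-home control or taken out of the target-home group. The change should be made, but it is not a condition for the study's planned comparison to stand. The sentence also covers unwilling staff; this point is confined to residents.

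**What to change.** Replace the option for residents with a statement on four points:
1. Residents who decline are not used as a control for the effect analysis.
2. They are not pooled with the waiting-home control.
3. The main comparison analyses consenting, assessed residents by home, including target-home residents who do not exercise.
4. If refusers are reported, they appear as a separate exploratory and descriptive group, by home and period, with their exposure to trained staff stated.

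The cost is a sentence or two. No new data are needed, since residents who do not exercise can already be assessed. The price is a smaller control pool and a somewhat diluted main contrast, by the factor 1 − g(1 − s) under the assumptions above. In exchange, that contrast does not depend on who was willing to train within the target home.
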